### Stakeholder acceptability

Acceptability of the intervention will be evaluated by patients and clinicians using a Likert scale modeled on the Theoretical Framework of Acceptability (version 2) [22]. These questionnaires have been reviewed for face validity by an expert panel including ROs, medical physicists, and radiation therapists. See Additional file 1: Appendix A for Questionnaire Items based on the Theoretical Framework of Acceptability.

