#### Patient acceptability

Patient acceptability will be assessed immediately following treatment delivery.

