#### Clinician acceptability

Clinical acceptability will include all those involved in the treatment pathway and will be assessed within 5 working days of treatment delivery *for Arm 2 patients only*. Clinicians may be asked to complete the questionnaire up to 3 times to inform analysis as to whether perceptions change over time, for example, with increasing familiarity/exposure to the novel workflow.

Involved clinicians will be identified by the Collaborating Investigator or a member of the Lawson Health Research Institute Clinical Research Unit based on the electronic care path/treatment record.

On a clinician’s first encounter, an electronic version of the Clinician LOI/Consent will be emailed to their institutional email address. All staff will be aware of the possibility of receiving the LOI/Consent as they will be informed prior to opening the study at a staff meeting/inservice and by an email from the Principal and Collaborating Investigator. If/when the e-consent is completed and received, an e-version of the questionnaire will then be sent to the clinician.

Clinicians will be required to indicate how many times they have previously participated in the dCT-enabled treatment planning workflow on the questionnaire, but will only be required to complete one e-consent form. They will be advised of their right to withdraw participation at any time and for any reason, and that completing one questionnaire does not obligate them to complete further questionnaires.

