### Sample size calculation

Based on a review of recent same-day treatments at the London Regional Cancer Program (LRCP), the estimated TIC in the standard arm of this trial will be 4.8 hours, with a standard deviation of 2. We hypothesize that in the experimental arm, the estimated TIC will be 2.5 hours, with the same standard deviation. Using a two-sided, two-sample t-test, with a 1:2 randomization, alpha of 0.05 and power of 80%, adjusting for 10% dropout, 33 patients are required, 11 in the standard arm and 22 in the experimental arm.

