### Statistical analysis plan

Patients will be analyzed in the groups to which they are assigned (intention-to-treat). Comparisons between treatment arms for TIC (primary endpoint) will be performed using the two-sample t-test. TIC data is anticipated to be normally distributed. In the event such data is not normally distributed, non-parametric testing using the Wilcoxon rank sum test will be substituted as appropriate. For the secondary endpoints for efficacy (rate of plan deliverability and rate of plan acceptability on blinded review of dose distributions) and acceptability (stakeholder evaluations based on Likert scale), differences between treatment arms will be compared using the Chi-square test or Fisher’s exact test as appropriate. For the secondary endpoint for scalability based on the ISAT, differences between treatment arms will be compared using the two-sample t-test or substituted with Wilcoxon rank sum test if such data is not normally distributed, similar to primary endpoint.

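### Patient Likert acceptability is compared between arms with tests that ignore the order of the responses, although a rank test is already named in the same paragraph

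*Protocol article*

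**What the plan says.** Under Statistical analysis plan, the article groups three secondary endpoints (plan deliverability, plan acceptability on blinded review, and stakeholder acceptability) and gives them one method. For the last of these it reads: "acceptability (stakeholder evaluations based on Likert scale), differences between treatment arms will be compared using the Chi-square test", with Fisher's exact test as the alternative. The same paragraph names the Wilcoxon rank sum test as the fallback for time in centre (TIC) and for the scalability tool, but not for the Likert data.

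The section Stakeholder acceptability says that patients and clinicians both answer a Likert questionnaire built on the Theoretical Framework of Acceptability. The items are in an additional file that is not shown. The article states no number of levels, total score or cut-point.

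The two groups of respondents differ in what can be compared:

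- **Patients:** "Patient acceptability will be assessed immediately following treatment delivery", with no restriction to one arm.
- **Clinicians:** their acceptability "will be assessed within 5 working days of treatment delivery", but for Arm 2 patients only.

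Under Sample size calculation, "33 patients are required, 11 in the standard arm and 22 in the experimental arm". That number rests on TIC alone.

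**The concern.** A Likert scale carries order, and the question asked of it has a direction: is the diagnostic-CT workflow rated better or worse than CT simulation? A chi-square or Fisher test on the full set of categories answers a different question, namely whether the two distributions differ in any way. If the response labels were shuffled, the p-value would not change. A significant result would not by itself say which arm patients preferred, and part of the information in a small sample would go unused.

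Acceptability is one of the three stated objectives, and the patient questionnaire is the only part of it with data in both arms. With about 33 respondents there is little power to give away. The paragraph also offers a rank test for endpoints whose normality is only in doubt, and withholds it from one that is ordinal by construction.

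**Working it through.** **1. The plan's own figure.** Inputs from Sample size calculation: means 4.8 and 2.5 hours, common SD 2, two-sided alpha 0.05, power 80%, ratio 1:2, 10% dropout. The difference is 4.8 − 2.5 = 2.3 hours. For the t-test the noncentrality is 2.3 / (2 × √(1/n₁ + 1/n₂)).

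- 9 + 18: power 0.773
- 10 + 20: noncentrality 2.3 / (2 × √0.15) = 2.97, power 0.818
- 11 + 22: power 0.855

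So 30 evaluable patients are needed, and 30 × 1.1 = 33. (Dividing, 30 / 0.9 = 33.3, would give 34.) The stated 33 reproduces. No power is stated for the Likert endpoint. The patient comparison is therefore about 11 versus 22, or 10 versus 20 after dropout.

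**2. Why order is lost.** Pearson's statistic is Σ (observed − expected)² / expected, with expected = arm total × category total / N. It is a sum over cells, so reordering the categories leaves it unchanged. The same holds for Fisher's test extended to more than two categories (Freeman-Halton), which ranks tables by their probability. The Wilcoxon statistic sums ranks and does depend on the order.

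**3. What this costs in power.** The article supplies no inputs, so everything here is assumed: a five-level item, two-sided 0.05, and a shift between arms.

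*First scenario.* Arm 1 probabilities are 0.07, 0.16, 0.27, 0.32, 0.18. Arm 2 is shifted upward on a latent normal scale, with 11 versus 22 patients. Permutation chi-square is set against the tie-corrected Wilcoxon test.

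| Shift (SD) | Chi-square | Wilcoxon | Loss (points) |
|---|---|---|---|
| 0.3 | 9% | 12% | 3 |
| 0.5 | 17% | 24% | 7 |
| 0.8 | 37% | 50% | 13 |
| 1.0 | 52% | 66% | 14 |
| 1.2 | 69% | 81% | 12 |

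*Other distributions.* Proportional-odds shifts with odds ratios 3, 4, 6 and 8, four assumed Arm 1 distributions, 11 versus 22, 2,000 simulated trials each. The Monte Carlo standard error of a single power is at most √(0.25 / 2000) = 1.1 points.

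| Arm 1 distribution | Wilcoxon minus chi-square (points) | Exact Wilcoxon minus exact Fisher (points) |
|---|---|---|
| Symmetric | 15–21 | 11–16 |
| Uniform | 16–19 | 9–13 |
| Moderate ceiling | 11–16 | 6–9 |
| Strong ceiling | 7–10 | 2–3 |

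Example (uniform, odds ratio 4): chi-square 0.36, Fisher 0.41, Wilcoxon 0.54. At 10 versus 20 the ranges are about 8–21 points over chi-square and 1–16 over Fisher. The smallest single gap is 0.539 − 0.534 = 0.005. A further set of scenarios that also varied the direction of the shift gave about 0 to 28 points.

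**4. Type I error.** With no difference between arms at 11 versus 22, rejection rates were 3.2–4.5% for chi-square, 4.2–5.8% for Fisher and 3.7–4.9% for Wilcoxon. Part of the gap to chi-square reflects its slight conservatism, so exact against exact is the fairer comparison.

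**The case against.** Several points on the other side are sound.

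- **The tests are valid.** The error rate is controlled. The endpoint is secondary and unpowered in a self-described feasibility trial, and the stopping rule uses plan deliverability, not acceptability. This stands and limits the weight of the point.
- **The loss can be negligible.** Near a strong ceiling, which is plausible for satisfaction-type items, exact Fisher loses only about 2–3 points. At a shift of 0.3 SD both tests have very low power. This also stands: a rank test does not make the endpoint well powered for modest effects.
- **A reader might infer a fixed loss of 11 to 14 points.** The documents do not support that. It is what one assumed mid-scale distribution with shifts of 0.8–1.2 SD gives, and other equally admissible assumptions give much less or more.
- **A reader might infer that sparse cells make the analysis unsound.** They do not, because the plan already allows Fisher's exact test.
- **The items might be dichotomised.** Fisher or chi-square would then fit the resulting binary outcome. The article states no cut-point, so this cannot be assumed. An assumed top-two-of-five split would cost about 10 to 53 points against the exact Wilcoxon in the same proportional-odds scenarios.
- **Naming a test does not rule out showing distributions by arm.** True, so direction could still be read from a table. The named test would still not assess it.

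The article's wording leaves a choice only between two tests that both ignore order, so it does not answer the point.

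**Conclusion.** The point holds as one of efficiency and interpretation, not validity. The plan assigns an ordered patient outcome to tests that ignore order and do not show which arm is rated higher. Under shift alternatives at 11 versus 22 these tests usually have less power than a rank test. With an assumed five-level item the loss lies between about 0 and over 20 points. That range depends on the assumed distribution, the size and direction of the shift, and the choice of chi-square or Fisher, none of which the documents give.

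The point concerns patients only. The promised between-arm comparison of clinician responses cannot be made at all, since there are no Arm 1 clinician data. The primary endpoint and the sample size are unaffected.

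**What to change.** In the Statistical analysis plan paragraph:

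- Compare patient Likert items, or a total score if one is formed, between arms with the Wilcoxon rank sum test already named there.
- Report the probability that an Arm 2 patient rates higher than an Arm 1 patient, counting ties as one half, with a 95% CI.
- Keep chi-square or Fisher's exact test for binary outcomes.
- State that clinician questionnaires are summarised descriptively, because they are collected for Arm 2 only.

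Stratifying the rank test by target group is optional. The plain test already cures the defect, and the power figures above are for the unstratified version.

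The cost is a sentence or two of text, with no new data and no change in sample size. The small downside is that a rank test is less sensitive to differences that are not a shift, such as one arm's responses splitting towards both ends of the scale. Tabulating the full response distribution by arm would show these.

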#### Plan deliverability

Plan deliverability will be reported as either yes or no. *Primary Plan Deliverability* will refer to the deliverability of the diagnostic-CT-enabled treatment plan. *Secondary Plan Deliverability* will refer to the deliverability of the CBCT-based plan in cases where a CBCT-based plan is generated.

For any undeliverable plan, the RO must document the reasons why the plan was undeliverable and the PI must be alerted within 24 hours.

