### Scalability

Scalability will be determined by the outcome of program leadership’s evaluation of the completed ISAT [23]. The ISAT will be completed by stakeholders involved in the provision of the Arm 2 workflow and will include representation from RO, Medical Physics, Radiation Therapy (CT and Treatment Delivery) and Trial Investigators. The assessment will be submitted to program leadership and rated for scalability. Possible recommendations include: (i) Merits scale up, (ii) Promising, but further information/planning is warranted, and (iii) Does not merit scale up.

For the purpose of this trial, “scaling up” would include dosimetric calibrations of regional affiliate’s diagnostic imaging machines to enable expanded patient eligibility.

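### The ISAT and clinician questionnaires are collected for Arm 2 only, so the between-arm tests stated for them have no Arm 1 data; plan deliverability has no Arm 1 definition

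*Protocol article*

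**What the plan says.** The Statistical analysis plan section of the protocol gives every secondary endpoint a comparison between arms. For scalability: "For the secondary endpoint for scalability based on the ISAT, differences between treatment arms will be compared using the two-sample t-test", or a Wilcoxon rank sum test if the data are not normal. For deliverability, plan acceptability and stakeholder acceptability: "differences between treatment arms will be compared using the Chi-square test or Fisher’s exact test as appropriate".

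The sections that define and collect these outcomes read differently:

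- **Scalability.** "The ISAT will be completed by stakeholders involved in the provision of the Arm 2 workflow". The endpoint itself is a leadership judgement: "Scalability will be determined by the outcome of program leadership’s evaluation of the completed ISAT". That judgement has three levels: "Possible recommendations include: (i) Merits scale up, (ii) Promising, but further information/planning is warranted, and (iii) Does not merit scale up".
- **Clinician acceptability.** Questionnaires go out "for Arm 2 patients only", and one clinician may answer up to three times. The Clinician inclusion criteria admit only staff who worked on an Arm 2 patient.
- **Plan deliverability.** The primary version "will refer to the deliverability of the diagnostic-CT-enabled treatment plan". The secondary version concerns the CBCT-based plan, where one is made.

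**The concern.** A two-sample test needs observations in both samples. For the ISAT and the clinician questionnaires the protocol's own collection rules produce none in Arm 1. For deliverability, the two named versions describe plans that only Arm 2 patients receive.

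The research hypothesis is that the workflow is effective, acceptable and scalable. As written, the scalability claim has no analysis that can be carried out, and the clinician part of acceptability has none either. Whoever analyses the trial would have to choose a replacement after seeing the data. For deliverability the risk is different. If an Arm 1 rate is supplied to make the test possible, a non-significant Fisher result could be taken as evidence that the two workflows deliver equally well, which a sample of 11 and 22 cannot show.

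**Working it through.** **1. The plan's own figure.** Inputs from Sample size calculation: means 4.8 h and 2.5 h, SD 2, two-sided alpha 0.05, power 80%, ratio 1:2, dropout 10%. Standardised difference d = (4.8 − 2.5)/2 = 1.15. The exact (noncentral t) calculation gives 9.59 in the standard arm, rounded up to 10, so 10 + 20 = 30. Allowing for dropout, 30 × 1.1 = 33, split 11 and 22. The stated 33 is reproduced. It rests on time in centre alone, so nothing below affects it.

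**2. Each stated test against the data collected.**

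| Outcome | Stated between-arm test | Arm 1 data under the protocol's own rules |
|---|---|---|
| ISAT (Scalability) | t-test or Wilcoxon | None: one assessment, of the Arm 2 workflow |
| Clinician questionnaires (Clinician acceptability; Clinician inclusion criteria) | Chi-square or Fisher | None: Arm 2 only |
| Plan deliverability | Chi-square or Fisher | None under the two named definitions; a generic yes/no is possible |
| Plan acceptability | Chi-square or Fisher | Available: fraction 1 CBCT is required in both arms |
| Patient questionnaires (Patient acceptability) | Chi-square or Fisher | Available: not restricted by arm |

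**3. ISAT.** The t statistic divides the difference in means by s·√(1/n₁ + 1/n₂). With n₁ = 0 neither the Arm 1 mean nor 1/n₁ exists, and a rank sum test fails for the same reason. The measurement level does not fit either: the endpoint is one programme-level category out of three.

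**4. Clinician acceptability.** The Secondary endpoints section counts radiation oncologists, therapists and physicists among the stakeholders, and the analysis text covers "acceptability (stakeholder evaluations based on Likert scale") without limiting it to patients. With no Arm 1 clinicians, only the patient questionnaires can enter a between-arm table.

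**5. Deliverability, if an Arm 1 yes/no were recorded.** Assume Arm 1 is 11/11. This figure is not in the protocol. With f failures, all in Arm 2, the hypergeometric probability of the observed table is C(22, f)/C(33, f). The two-sided p adds every table that is no more probable.

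- 14/22 (f = 8): the observed table has 319,770/13,884,156 = 0.0230. Tables with 6, 7 or 8 failures in Arm 1 add (106,722 + 7,260 + 165)/13,884,156 = 0.0082. p = 0.031.
- 15/22 (f = 7): the observed table has 170,544/4,272,048 = 0.0399. Tables with 5, 6 or 7 failures in Arm 1 add (106,722 + 10,164 + 330)/4,272,048 = 0.0274. p = 0.067.
- 18/22 gives p = 0.28, 20/22 gives 0.54 and 21/22 gives 1.00.

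The test therefore crosses 0.05 only at 14/22 = 64% or lower. That is close to the 60% at which the interim rule allows the team to recommend stopping.

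**6. What Arm 2 alone can show.** Exact (Clopper-Pearson) 95% limits for x/22 are the 2.5% quantile of Beta(x, 23 − x) and the 97.5% quantile of Beta(x + 1, 22 − x). For x = 22 the lower limit reduces to 0.025^(1/22) = 0.846 and the upper limit is 1.

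| Deliverable | 95% interval |
|---|---|
| 22/22 | 84.6% to 100% |
| 21/22 | 77.2% to 99.9% |
| 20/22 | 70.8% to 98.9% |
| 18/22 | 59.7% to 94.8% |

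**The case against.** The strongest reply concerns deliverability. The Plan deliverability section opens generically with a yes/no report and asks for reasons for any undeliverable plan. The interim rule speaks of the Arm 2 rate, a qualifier that would be redundant if no other arm had one. Arm 1 patients also have a mandatory CBCT at fraction 1, so progression or new findings could be seen there too. All of this stands. A reader might infer that deliverability, like the ISAT, has zero Arm 1 observations; the text does not establish that. What it does show is a missing Arm 1 definition: both named versions refer to Arm 2 plans, the undeliverability criteria sit under Arm 2, and the Background ties deliverability to the experimental planning arm.

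A reader might also infer that most of the secondary endpoints cannot be analysed. That goes too far. Of the four listed, plan acceptability can be compared, and so can the patient part of stakeholder acceptability.

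Nor does the protocol prescribe a chi-square test within Arm 2 that treats a clinician's repeat answers as independent. It says the repeats are there to look at change with familiarity, and it records exposure. Leaving the model for that to a fuller plan is ordinary practice.

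Finally, an analysis plan not shown here may handle these outcomes sensibly. That does not remove the point, because the protocol names the tests. The phrase about appropriateness governs chi-square versus Fisher, not whether the arms are compared.

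**Conclusion.** The point holds in bounded form. Two stated comparisons contradict the protocol's own data collection: the ISAT test cannot be run at all, and the stakeholder test cannot include clinicians. Neither conclusion needs any assumption. For deliverability, the defect is an endpoint without an Arm 1 definition, so the stated comparison has nothing specified to compare with. The 14/22 threshold depends on assuming 11/11 in Arm 1. It shows only that a non-significant test would not demonstrate comparable deliverability; the protocol itself does not say it would be read that way. Time in centre, the sample size of 33 and the interim rule, which uses an Arm 2 rate and no test, are untouched. The text should be corrected before analysis so that the replacement is not chosen after the results are known.

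**What to change.** Amend the Statistical analysis plan section as follows.

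- **ISAT:** delete the between-arm test. Report the leadership category, with item scores, descriptively.
- **Stakeholder acceptability:** restrict the between-arm test to patient questionnaires. Summarise clinician responses within Arm 2 by exposure number, without treating repeat answers from one clinician as independent. No particular model is needed, since the number of clinicians is not given.
- **Deliverability:** report Primary Plan Deliverability as a proportion of Arm 2 patients with an exact 95% interval, and show CBCT-plan deliverability separately, as the definitions already do. Keep a between-arm comparison only if an Arm 1 definition is added, and do not present a non-significant result as equivalence.
- **Unchanged:** between-arm tests for time in centre, plan acceptability and patient acceptability.

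The cost is wording only. No new data are needed unless the team chooses to define and record deliverability in Arm 1, which adds one yes/no item for the 11 patients planned there.

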## Adverse events

Arm 2 is not trialling a new treatment technique or dose/fractionation schedule and it is not anticipated to be associated with a higher risk of an adverse event or serious adverse event. As such, adverse event data will not be collected.

## Risks of participation

### Patient participant risks

Participation in this study does not increase the risk of experiencing the side effects of palliative radiation. Subjects in both study groups will receive the *same* type of radiation treatment. The *only difference* between groups is the type of CT imaging used to plan the treatment (CT simulation or diagnostic CT).

### Clinician participant risks/disadvantages

There are no anticipated risks related to participation as a clinician. Disadvantages for clinicians may include the time it takes or the inconvenience experienced in completing the questionnaire. Clinicians will not be compensated for their time, and completion of the survey will have no effect on employment, promotions, etc.

## Benefits

### Patient benefits

There is no guarantee of benefit in participating in this study. However, participants in Arm 2 may spend less time at the cancer centre than those in Arm 1.

### Clinician benefits

There is no guarantee of benefit in participating in this study, and completion of the survey will have no effect on employment, promotions, etc.

## Limitations

The investigation is non-blinded and participants will learn of both arms of the experiment during the consent process. This could introduce bias, specifically in relation to the perceived amount of time/effort required to participate (i.e. burden). A similar bias could manifest in the provider group as clinician’s who accrue may be inherently more enthusiastic about the novel workflow.

A qualitative approach using semi-structured interviews or focus groups would likely be a more comprehensive approach to assessing stakeholder acceptability. However, given the nature and timescale of the work, a quantitative, close-questioned survey, designed by the author and based on the TFA, was felt to be sufficient. Though the questionnaires will be reviewed by an expert panel of clinician-scientists for face-validity and by the appropriate Research Ethics Boards, the instrument will not undergo external validation.

While the phase II RCT design proposed herein will be limited in its degree of realizable internal validity compared to a highly powered phase III trial, it reasonably scaled to evaluate efficacy within a dissertation timeframe. Methods such as a structured protocol and carefully selected endpoints will allow for reliable and impactful statistical analysis, and randomization will provide rigor beyond a confirmatory cohort study and enable assessment of other facets of feasibility.

Convenience sampling will also limit the generalizability of results to larger/more heterogeneous populations. However, as eligibility is based on the type of radiation treatment participants will receive versus personal or disease characteristics, and as eligibility criteria are inclusive of many PRT patients, convenience sampling remains appropriate in this design.

